### Sample size

The sample size was determined using the power-based approach for the primary endpoint, assuming that the intervention may be adopted if H1: p > 50% (greater than 50% of consenting clinicians offer CIFeR to at least 1 patient at 3-months follow-up), and that H0: p < 30%, a level below which the intervention will not be regarded as adopted. If 30% is assumed for the participation rate under the null and 50% under the alternative, then based on a one-sided alpha = 5% and a power of 80%, the estimated sample size is n = 39. The intervention would be regarded as adopted, if at least 17 out of 39 clinicians offer CIFeR to at least 1 early stage/curable breast cancer patient by 3 months. Assuming a drop-out rate of 25% then 50 clinicians will need to be recruited to meet the primary endpoint of the study.

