### Statistical analyses

Measures of Proctor outcomes (e.g. intervention adoption, acceptability) will be reported using descriptive statistics including proportions, means and standard deviations. Baseline demographics will be summarized in table format. Repeated measure t-tests will be used to examine changes in oncologist self-efficacy scores pre- and post-intervention. Proctor outcomes will be summarised using descriptive statistics. Exploratory predictors of higher adoption rates will be examined using linear models. Kolmogorov-Smirnov and Shapiro-Wilk tests of normality (tests statistic, degrees of freedom, p-value) will be performed.

As there are no pre-specified instructions available for handling missing data for the SE-12, the averages for the remaining items for the scale in question will be calculated with the adjusted denominator. Missing data from the questionnaires will be descriptively reported and all available data will be included for analysis.

Qualitative data will be analysed using Framework analysis [19]. Line-by-line coding will be conducted on three transcripts by the research team to develop the preliminary coding framework, which will be iteratively refined following review of subsequent transcripts. Over-arching themes and sub-themes will be developed to summarize the data. Differences in researcher interpretation of the data will be resolved through discussion. Themes arising from medical and radiation oncologists and surgeons will be compared. We will use the consolidated criteria for reporting qualitative research (COREQ) to guide reporting [20].

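### At the stated 25% drop-out, 39 evaluable clinicians need 52 recruits, not 50; with 50, exact power is about 74–79% rather than 80% (minor)

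*Protocol article*

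**What the plan says.** The Sample size section of the protocol article sets the rates: "If 30% is assumed for the participation rate under the null and 50% under the alternative". It continues: "based on a one-sided alpha = 5% and a power of 80%, the estimated sample size is n = 39". Adoption is to be declared if "at least 17 out of 39 clinicians offer CIFeR to at least 1 early stage/curable breast cancer patient by 3 months". The recruitment target follows: "Assuming a drop-out rate of 25% then 50 clinicians will need to be recruited to meet the primary endpoint of the study". The inflation formula is not shown, and no cutoff is given for any evaluable number other than 39. Under Statistical analyses, the article says of questionnaire data that "all available data will be included for analysis", so the number analysed will be whatever number responds.

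**The concern.** Three figures in one section (39 evaluable, 25% drop-out, 50 recruited) should be linked by simple division, and they are not. The target of 50 is what one would get by adding 25% to 39 (48.75) and rounding up, rather than dividing by the retained fraction; the article does not say how it was obtained. If drop-out runs as assumed, the primary analysis will have fewer than the 39 clinicians on which the stated power rests.

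A second question follows. The success count of 17 is tied to 39, so one must ask whether it remains a valid 5% rule at the number the plan implies, and what rule applies if a different number respond.

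**Working it through.** **Inputs**, all from the Sample size section: null rate 0.30, alternative 0.50, one-sided alpha 0.05, power 0.80, evaluable n = 39, cutoff 17, drop-out 0.25, recruitment target 50.

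**1. Reproduce the plan's own figures.** With X ~ Binomial(39, p):
- alpha = P(X ≥ 17 | p = 0.30) = 0.04998
- power = P(X ≥ 17 | p = 0.50) = 0.832

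So 39 and 17 reproduce with an exact one-sample binomial test. Searching upward from n = 34, 39 is the smallest n with exact alpha at most 5% and power at least 80%.

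**2. Drop-out inflation.**
- Recruits needed: 39/(1 − 0.25) = 52
- Expected evaluable from 50: 50 × 0.75 = 37.5
- Drop-out at which 50 yields 39: 1 − 39/50 = 22%
- For comparison: 39 × 1.25 = 48.75

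**3. Operating characteristics at the number implied by 50 recruits.**

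| Evaluable n | Exact 5% cutoff | Alpha | Power at 50% | Alpha with cutoff one lower |
|---|---|---|---|---|
| 36 | 16 | 4.7% | 79.7% | 9.2% |
| 37 | 17 | 2.9% | 74.4% | 6.0% |
| 38 | 17 | 3.9% | 79.1% | 7.6% |
| 39 | 17 | 4.998% | 83.2% | 9.4% |

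At 37 and 38, 17 is the right cutoff: 16 would exceed 5%.

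**4. Averaging over random drop-out.** Assume each recruit is lost with probability 0.25, independently of adoption. The article does not state this.
- Fixed bar of 17 observed adopters: X ~ Binomial(N, 0.75p). With N = 50, power is P(X ≥ 17 | 0.375) = 74.2% and alpha is P(X ≥ 17 | 0.225) = 4.2%. With N = 52, power is 80.4% and alpha 6.0%.
- Exact cutoff chosen for the number analysed: power is 77.7% with N = 50 and 79.1% with N = 52.

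Under the same assumption, 50 recruits yield 39 or more evaluable clinicians with probability 38%.

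**5. Cutoffs for other numbers analysed** (smallest r with P(X ≥ r | n, 0.30) ≤ 0.05):

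| Number analysed | Cutoff |
|---|---|
| 36 | 16 |
| 37–39 | 17 |
| 40–41 | 18 |
| 42–44 | 19 |
| 45–47 | 20 |
| 48–50 | 21 |

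Alpha at 39 is already 4.998%, so the count of 17 cannot be carried upward: at n = 40 it would give 6.3%.

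**The case against.** The strongest reply is that the slip is two clinicians in 52 and the power loss is barely material. Much of this stands. The sample of 39 carries a reserve (83.2%), and 79.1% at 38 is close to the stated 80%. The 74.4% at 37 owes a good deal to binomial discreteness, since 36 clinicians with a cutoff of 16 give 79.7%. With cutoffs matched to the number analysed, recruiting 50 instead of 52 costs only about 1.4 points on average (77.7% against 79.1%). Recruitment was also finishing when the article appeared, so a larger target may no longer be practical.

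A reader might go further and infer that the shortfall undermines the cutoff of 17 or inflates type I error. The article does not support that. At 37–38 evaluable clinicians the cutoff is exact and alpha is below 5%; averaged over 25% drop-out from 50, a fixed bar of 17 gives about 4.2%. Keeping 17 at 45 or 50 respondents would give alpha of about 16% or 32%, but that needs retention far better than planned and a rule the article never states.

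It can also be said that cutoffs for other sample sizes belong in the analysis plan, which is not shown. That is fair, and it is why the table is only an accompaniment to the correction. The objection leaves the arithmetic untouched: 39, 25% and 50 stand together in one section and cannot all be right.

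**Conclusion.** The point holds as a minor error. At 25% drop-out the target should be 52; 50 allows for 22%. With 50 recruits and the planned loss, 37 or 38 clinicians are evaluable, the cutoff of 17 remains valid (alpha 2.9–3.9%), and exact power is about 74–79%, modestly below 80%.

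The power figures assume the exact binomial test, which reproduces the plan's own 39 and 17, and rates of 30% and 50% among those analysed. The averaged figures further assume that drop-out is unrelated to adoption.

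A separate and larger inconsistency affects any cutoff: the Primary outcome section declares adoption at 50% or more observed, which is 20 of 39, while the Sample size section declares it at 17 of 39 (43.6%). At a true rate of 50%, requiring 20 of 39 gives power of 50%. That conflict does not arise from the drop-out slip, but it must be settled before cutoffs are tabulated.

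**What to change.** 1. Correct the last sentence of the Sample size section in one of two ways: state that 50 recruits allow for 22% drop-out, or state that 25% drop-out needs 52 recruits and that with 50 the exact power is about 74–79%.
2. Reconcile the 17-of-39 rule with the 50% observed-adoption rule under Primary outcome, so that one decision rule applies.
3. If the exact-test rule is kept, state the denominator and give the cutoff by number analysed, as tabulated in the working, fixed before the primary result is seen.

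The cost is one corrected sentence and a short table. The stated power becomes slightly less favourable, and no extra recruitment is needed.

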### Data handling

Study data will be recorded on the password protected Qualtrics server. All required data entry fields will be completed. All completed questionnaires, audio-recordings and transcripts will be managed centrally at the University of Sydney. Electronic data will be collected securely by the Qualtrics database, and only the chief investigator or site principal investigator will have access to the study data. All information will be stored securely for seven years as per NHMRC and will only be available to staff directly involved with the study.

Non-identified data will be analysed by the core research team (chief investigator, principle investigator and sub-investigators), with the possible assistance of additional research staff or research students. A Clinical Study Report will be issued which may form the basis of a manuscript intended for publication.

All data collected for, used in, or generated by this project will be disposed by secure methods after seven years from the completion of the study. Paper files will be shredded and computer files will be deleted. Any major changes to the protocol will be updated to participants and relevant ethics committee.

### Statistical analyses

Measures of Proctor outcomes (e.g. intervention adoption, acceptability) will be reported using descriptive statistics including proportions, means and standard deviations. Baseline demographics will be summarized in table format. Repeated measure t-tests will be used to examine changes in oncologist self-efficacy scores pre- and post-intervention. Proctor outcomes will be summarised using descriptive statistics. Exploratory predictors of higher adoption rates will be examined using linear models. Kolmogorov-Smirnov and Shapiro-Wilk tests of normality (tests statistic, degrees of freedom, p-value) will be performed.

As there are no pre-specified instructions available for handling missing data for the SE-12, the averages for the remaining items for the scale in question will be calculated with the adjusted denominator. Missing data from the questionnaires will be descriptively reported and all available data will be included for analysis.

Qualitative data will be analysed using Framework analysis [19]. Line-by-line coding will be conducted on three transcripts by the research team to develop the preliminary coding framework, which will be iteratively refined following review of subsequent transcripts. Over-arching themes and sub-themes will be developed to summarize the data. Differences in researcher interpretation of the data will be resolved through discussion. Themes arising from medical and radiation oncologists and surgeons will be compared. We will use the consolidated criteria for reporting qualitative research (COREQ) to guide reporting [20].

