The resulting data will guide further intervention development, and future large-scale efficacy studies. This sequence of research is recommended by Proctor et al. [15] who position implementation outcomes as preceding both service outcomes and client outcomes, with the latter outcomes being impacted by implementation outcomes. The PARiHS framework (Promoting Action on Research Implementation in Health Services) [16] incorporating strong scientific evidence with a supportive context and implementation facilitation will be used to guide the study.

The primary hypothesis of CIFeR_2 is that:

> 50% of participating Medical and Radiation oncologists or surgeons will offer CIFeR to at least 1 early stage/curable breast cancer patient by 3 months after receiving training.

Secondary hypotheses are that:

2.> 50% of participating Medical and Radiation oncologists or surgeons will offer CIFeR to at least 1 early stage/curable breast cancer patient in the last 3 months when surveyed 6-months after their training on the CIFeR intervention.3.More than 20% of Medical and Radiation oncologists or surgeons invited to join the CIFeR implementation study will agree to participate.4.Participating Medical and Radiation oncologists or surgeons will deliver 4/5 of the components of CIFeR (80% fidelity) to at least two of the first three patients to whom they deliver CIFeR.5.Participating Medical and Radiation oncologists or surgeons will find CIFeR acceptable, appropriate and feasible in routine practice.6.CIFeR implementation will be low in costs across consultation time, resources, and psychologist referrals.7.Participating Medical and Radiation oncologists or surgeons will report a range of barriers and facilitators to CIFeR implementation in qualitative interviews at 6 months follow-up.8.There will be no differences between Medical and Radiation oncologists and surgeons with respect to CIFeR implementation outcomes.9.Oncologists’ or surgeons’ scores on a scale assessing self-efficacy to manage FCR in patients will increase from baseline to post-training, and to 3 and 6-months post-training follow-up.

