#### Primary outcome

The primary outcome of the CIFeR_2 study is adoption (percentage of participating oncologists or surgeons who report offering the CIFeR intervention to at least one early stage/curable breast cancer patient attending a follow-up appointment 3 months after receiving the CIFeR training). The CIFeR intervention will be defined as adopted if ≥ 50% of oncologists or surgeons deliver the CIFeR intervention to at least one early stage/curable breast cancer patient in that timeframe, whereas the intervention will be deemed not adopted if < 50% of oncologists deliver CIFeR in that timeframe.

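### Secondary hypothesis 8 predicts no differences between specialties, without a margin, in a sample too small to support it; separately, linear models do not suit predictors of a yes/no adoption outcome

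*Protocol article*

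**What the plan says.** Among the secondary hypotheses at the end of the Background section, number 8 reads: "There will be no differences between Medical and Radiation oncologists and surgeons with respect to CIFeR implementation outcomes". No margin is given, and the article does not say how many clinicians of each specialty are expected.

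The Sample size section states its purpose: "The sample size was determined using the power-based approach for the primary endpoint". Its inputs are "If 30% is assumed for the participation rate under the null and 50% under the alternative", and "based on a one-sided alpha = 5% and a power of 80%, the estimated sample size is n = 39". Success is "at least 17 out of 39 clinicians offer CIFeR to at least 1 early stage/curable breast cancer patient by 3 months". On recruitment it says: "Assuming a drop-out rate of 25% then 50 clinicians will need to be recruited".

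The Primary outcome section defines adoption as the "percentage of participating oncologists or surgeons who report offering the CIFeR intervention to at least one early stage/curable breast cancer patient" by 3 months, which is a yes or no for each clinician. Statistical analyses reports the Proctor outcomes descriptively and compares the specialties explicitly only for interview themes. On predictors it says: "Exploratory predictors of higher adoption rates will be examined using linear models". Tests of normality are named in the next sentence.

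**The concern.** A hypothesis of no differences without a margin is a hypothesis of exact equality, which no data can establish. It can only appear to be supported when no difference is seen. In a sample of about 39 divided among two or three specialties, that will often happen when true differences are large. At stake is what the study may conclude about whether adoption, acceptability, feasibility and the other outcomes carry over from one specialty to another.

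The predictor analysis raises a separate and smaller question. A linear model for a 0/1 outcome works on a scale that does not respect the limits of 0% and 100%. The article does not say whether adoption, as it defines it, is really the outcome to be modelled.

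**Working it through.** **Inputs.** From Sample size: null 30%, alternative 50%, one-sided 5%, power 80%, 39 evaluable, cut-off 17, drop-out 25%, 50 recruited. From Primary outcome: adoption is yes/no per clinician. Assumed, because the article does not state them: the split by specialty, the true adoption rates and any margin.

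**1. The plan's own figure.** Exact binomial: P(X ≥ 17 | n = 39, p = 0.30) = 0.04998 and P(X ≥ 17 | n = 39, p = 0.50) = 0.832. No smaller n meets both 5% and 80%, so 39 and 17 reproduce. Drop-out gives 39 / (1 − 0.25) = 52 against the stated 50, a gap that does not bear on this point. Nothing in the calculation concerns a comparison between specialties.

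**2. Precision and power for two groups.** At 50% adoption the 95% half-width is 1.96 × √(0.25/n₁ + 0.25/n₂). For 13 v 13 this is 1.96 × √(0.5/13) = 0.384. Power is for Fisher's exact test, two-sided 5%, by full enumeration, with the higher rate in the group named first.

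| Assumed split | Basis | Half-width (points) | Power, 70% v 40% | Power, 50% v 30% |
|---|---|---|---|---|
| 13 v 13 | 39 in equal thirds | 38 | 26% | 12% |
| 17 v 17 | all 50 evaluable, in thirds | 34 | 31% | 14% |
| 20 v 19 | 39, oncologists pooled v surgeons | 31 | 39% | 19% |
| 26 v 13 | 39, two thirds v one third | 33 | 35% | 18% |
| 25 v 7 | 39, uneven (25/7/7) | 42 | 25% | 9% |

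A true 30-point gap (70% v 40%) is therefore missed 61–75% of the time, and a true 20-point gap (50% v 30%) 81–91% of the time. At 70% adoption the 13 v 13 half-width is 1.96 × √(0.42/13) = 0.352, so 50% is the least favourable case, but not by much.

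**3. All three groups together.** A 3-group chi-square test with 13/13/13 has 13% power for adoption of 40/50/60% and 42% for 30/50/70%. A 25/7/7 split gives the same rounded figures.

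**4. Could a margin rescue the hypothesis at this size?** For two one-sided tests at 5% with 80% power and a true difference of zero, n per group = 2p(1 − p)(1.645 + 1.282)² / m². At p = 0.50 this gives 429, 108 and 48 per group for margins of 10, 20 and 30 points. With 13 per group, the power to show equivalence is 0% at a 20-point margin, 0–2% at 30 points and 31–44% at 40 points (the ranges cover adoption of 50% and 70%).

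**5. Predictor model.** At 50% adoption, 39 × 0.5 = 19.5, so about 19–20 clinicians fall in the smaller outcome class, which supports only a few predictors. With specialty as the only predictor, a linear model's fitted values are the group proportions and stay within 0–100%. With a strong continuous predictor they commonly leave that range. Simulated ordinary least squares on a yes/no outcome (39 clinicians in three groups of 13; 4,000 runs per rate; adoption 50%, 70%, 85%) gave type I error of 5.6%, 5.4% and 3.3% for one group against the rest, and 4.7%, 5.4% and 3.8% for the 3-group F test. Continuous or multiple predictors were not simulated.

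**The case against.** The strongest reply is that the article plans no test between specialties. Proctor outcomes are to be described, and a descriptive table by specialty would already be close to what is asked for here. Low power for a secondary hypothesis is usual when a study is sized on its primary endpoint, and a margin could stand in an analysis plan that is not shown. Most of this is fair, and the absence of a specialty test is not counted as a fault. But the hypothesis is stated in the article as an expected finding, and at this size even a 30-point margin could hardly be confirmed. The wording needs to change whatever the analysis plan contains.

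A reader might infer that the study would very likely report equal specialties when they differ, and that this would misdirect roll-out. The documents do not support either step. A descriptive plan does not commit the authors to that reading, and no section ties roll-out to specialty. The Background says the data will guide further intervention development and future large-scale efficacy studies.

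On the predictor analysis, 'linear models' may loosely include generalised linear models. Speaking of higher adoption rates may refer to the number of patients given CIFeR, which is also collected, and the normality tests may belong to the self-efficacy t-tests. The analysis is labelled exploratory. A reader might also infer that the linear model inflates false positives, but the simulation gives no sign of that. What remains is that the only definition of adoption in the article is yes/no per clinician, and a linear scale suits that poorly.

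**Conclusion.** Hypothesis 8 cannot be supported as written. Over the assumed splits, a difference in adoption would be known only to within about 31–42 points either side, and real gaps of 20–30 points would be missed about 61–91% of the time. Similar percentages or a non-significant test would be compatible with large differences. The split and the adoption rates are assumptions, but the conclusion is the same across the range shown, including all 50 clinicians evaluable and oncologists pooled against surgeons. The point is of moderate weight: it limits a secondary claim and leaves the primary endpoint and its sample size untouched.

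The model for predictors of adoption is a lesser matter. The fault is an unsuitable scale, possible fitted values outside 0–100% and an outcome that is not clearly named. Inflated type I error has not been shown.

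**What to change.** Restate hypothesis 8 as an estimation aim. Report adoption and each other yes/no outcome by specialty, with differences and 95% confidence intervals. Call the comparison inconclusive unless the interval lies inside a margin stated before the data are examined. At this size most comparisons will be inconclusive, and the plan should say so. The cost is a change of wording and giving up the claim of no difference; no extra data or recruitment is needed.

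For predictors, name the outcome. If it is adoption as defined under Primary outcome, use logistic regression, penalised (for example Firth's) at this sample size, with a few predictors named in advance and odds ratios with confidence intervals. If it is the number of patients given CIFeR, say so and use a count model. Either choice costs a sentence in the plan and a different software call.

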### Recruitment timeline

Recruitment has started as of March 2022 and recruitment is in process of finishing with final follow-up to be sent in May 2023.

## Discussion

### Theoretical significance

Given there are currently no clinician-delivered interventions to address FCR, the CIFeR_2 implementation study advances the field by representing and solidifying the evidence for the beneficial and appropriate use of a clinician-lead educational intervention for patient FCR within the context of follow-up clinics. Additionally, the current study will provide a guide of implementation efforts, as well as provide a greater understanding of the barriers and facilitators of implementing CIFeR in routine care. Implementation studies are increasingly being used to identify and address barriers early in implementation efforts, to ensure successful integration of evidence into practice [21].

